**Visits 2 and 3 (post hoc observations)**

(1)The investigator or sub-investigator will collect the blood for immunogenicity evaluation.(2)The investigator or sub-investigator will examine the study subjects and review the entries of the health diary (Visit 2 only).(3)In case the adverse event caused by KD-414 has not been resolved, the recovery and stabilization of symptoms must be confirmed (only if adverse events occur/continue).

**Visits 1–3 (public cost booster)**

Investigators will obtain informed consent if booster doses are to be administered to the healthcare workers in the future. Information on vaccinations will be received from the hospital. Personnel who do not receive vaccination in the hospital may be contacted individually.

(1)The investigator or sub-investigator will collect the blood for antibody titration.(2)Study subjects will receive a publicly funded supplemental coronavirus vaccine during Visit 1.(3)Study subjects immunized with the vaccine will be requested to complete a health diary.

**Survey items**

**Subject characteristics**

Information from previous study (*A survey of vaccine-induced COVID-19 antibody titer to verify temporal change*; NCGM Ethical Review Board Approval Number: NCGM-A-004175-04) should also be used.

(1)Work career (identification of COVID-19 practice engagement and working contacts with patients with COVID-19)(2)Attributes of study subjects (age, sex, occupation type, etc.)(3)Diseases and medications that may affect antibody production or the Th1/Th2 ratio (as appropriate)(4)Adverse reaction information (fever, malaise, etc.)(5)Medical examination data (anamnesis, antibody-equivalent to SARS-CoV-2) as appropriate(6)Content of vaccination questionnaire(7)History of BNT162b2 mRNA (date of receiving the first and second dose of vaccination)(8)Data from NCGM health survey after vaccination (conducted as a vaccination project)(9)Data from NCGM staff antibody surveillance on antibodies against SARS-CoV-2 (this study protocol supplemented with data provision for this study was approved by the Ethics Committee of the Center Hospital of the National Center for Global Health and Medicine, Tokyo, Japan.).

**Investigation items for efficacy endpoints**

(1)COVID-19 disease

**Investigation items for safety endpoints**

(1)Examination and measurement of body temperature(2)Health diary entry review

The investigator will request the study subjects to record some measurements in a health diary.

①Subaxillary temperature: The investigator measures and records the body temperature daily for seven days after inoculation with KD-414. The maximum body temperature should be recorded if more than one measurement is performed per day.②Inoculation site reaction: Study subjects must record the presence or absence of an inoculation site reaction daily for seven days after inoculation. In particular, the major axis should be measured and recorded if redness or swelling is observed at the inoculation site.③Subjective symptoms/objective findings: The study subjects should record any subjective symptoms or objective findings.

NOTE: If pyrexia is observed seven days after the inoculation, the body temperature measurement should be continued. The date on which the temperature decreases to <37.5 °C should also be recorded.

**Investigation items for immunogenicity endpoints**

(1)Timing of blood sampling: Visits 1 (before vaccine inoculation), 2, and 3.(2)Measurements:

Determination of neutralizing antibody titers against live SARS-CoV-2 viruses (on days 0, 7, and 40 post-inoculation and in the residual sample collected on days 7 and 40 in the previous studies; conducted at the Department of Refractory Viral Infections, National Center for Global Health and Medicine Research Institute, Tokyo, Japan).

①Determination of neutralizing antibodies (on days 0, 7, and 40 post-inoculation) against live SARS-CoV-2 virus (in residual samples collected on days 7 and 40 in previous studies; conducted by the Department of Refractory Viral Infections, National Center for Global Health and Medicine Research Institute, Tokyo, Japan) is shown in Table 4.

Three assays were performed to detect the IgM and IgG antibodies against SARS-CoV-2 spike protein (IgM-S and IgG-S, respectively) and IgG antibodies against SARS-CoV-2 nucleocapsid protein (IgG-N). The presence of IgG-N antibodies can indicate SARS-CoV-2 infection prior to the study and during follow-up, regardless of the BNT162b2 vaccination status. In contrast, the presence of IgM-S and IgG-S indicates previous infection and/or humoral immunity following BNT162b2 vaccination, because BNT162b2 is constructed to express the full-length spike protein.

②Antibody (IgG) titers against the viral nucleocapsid protein

The Abbott ARCHITECT^®^ SARS-CoV-2 anti-N IgG assay based on semi-quantitative CMIA was performed. Determination by reagent is shown in Table 4 (determination on days 0, 7, and 40 post-inoculation)

③Antibody (IgM) titers against viral spike proteins

The AdviseDx SARS-CoV-2 IgM assay, based on semi-quantitative CMIA, was performed using the Abbott ARCHITECT^®^ according to the manufacturer’s instructions. Determination by reagent is shown in Table 4.

④Antibody (IgG) titers against viral spike proteins

The AdviseDx SARS-CoV-2 IgG II assay was performed using the Abbott ARCHITECT^®^ following the manufacturer’s protocol. Determination by reagent is shown in Table 4.

⑤Flow cytometric analysis of Th1 and Th2 cells (in samples collected on day 7 post-inoculation) (outsourced to SRLs, Tokyo, Japan).

The percentage of Th1 (IFNγ^+^ and IL-4^−^) and Th2 (IFNγ^-^ and IL-4^+^) cells among CD4^+^ lymphocytes will be calculated.

⑥QuantiFERON SARS-CoV-2 RUO test (QIAGEN, Germany; performed on days 0 and 7 post-inoculation)

SARS-CoV-2 specific CD4^+^ and CD8^+^ T cell responses were investigated. We quantified T cell-produced interferon-gamma (IFN-γ) in response to SARS-CoV-2 spike peptides using QuantiFERON SARS-CoV-2 RUO (QIAGEN, Germany) according to the manufacturer’s instructions.

Volume of blood sampling: 17 mL for Visits 1 and 3 and 22 mL for Visit 2. In total, 56- and 33-mL blood samples were collected from subjects immunized with the study vaccine (KD-414) and unvaccinated subjects, respectively. In total, 56 mL was collected during immunization at public cost.

(1)Treatment method: The blood sample will be allowed to stand at room temperature for 30 min as a guide. After coagulation, the blood samples will be centrifuged at 3000 rpm for 10 min to obtain the serum. The serum will be stored at <−20 °C.(2)Labeling and transportation methods for storage containers of specimens: Labels will include the name of the study subject, subject identification code, time of blood sampling, and date of blood sampling. The labels will be attached to the sample storage container.

**Evaluation and documentation of adverse events**

(1)The investigator will record the following items on the case report form regarding adverse events in the study subjects from the date of vaccination to Visit 3 (post hoc observations).(2)Name of the adverse event(3)Day of adverse event onset(4)Severity of adverse event (see the section titled “Severity classification of adverse events”).(5)Seriousness of the adverse event (see the section titled “Reporting of diseases to the certified Clinical Research Review Board (research using unapproved or off-label drugs, etc.);”).(6)Treatment of the adverse event(7)Outcome (recovery (including remission), recovery but with sequelae, not recovered, death, unknown), and date of outcome(8)Causal relationship to the study vaccine (see the section titled “Causal relationship between study drugs and adverse events”).

**Acceptable therapies (including emergency care) before and during the study period**

The concomitant use of drugs required for symptomatic treatment is acceptable in the event of an adverse reaction associated with vaccination.

**Therapies prohibited before and during the**
**study period**

(1)Immunization with other COVID 19 vaccines is prohibited for 40 days post-KD-414 vaccination.(2)Other vaccines are not allowed for 7 days post-KD-414 vaccination.

**Clinical evaluation**

The relevant clinical guidelines from the WHO will be followed in relation to the clinical evaluation of the vaccine [9,10].

**Evaluation items**

**Primary endpoint**

Neutralizing antibody titers against SARS-CoV-2 on day 7 post-immunization

Rationale: Clinical trials evaluating the efficacy of SARS-CoV-2 vaccine candidates in preventing the development of COVID-19 should be conducted. However, a long study period is required to assess the onset of preventive effects, which is not practical as this is an exploratory study. To investigate the need for a large validation study, the immunogenicity-related parameters, including neutralizing antibody titers, will be evaluated as an important endpoint in this study. The primary assessment time point in this study is day 7 post-immunization as the highest titer was observed at this time point in the previous study.

**Secondary endpoint**

<Immunogenicity>

(1)Titers of neutralizing antibodies against SARS-CoV-2 on day 40 post-inoculation(2)IgG antibodies against SARS-CoV-2 spike protein (IgG-S) on days 7 and 40 post-inoculation(3)IgG antibodies against SARS-CoV-2 nucleocapsid protein (IgG-N) on days 7 and 40 post-inoculation(4)IgM antibodies against SARS-CoV-2 spike protein (IgM-S) on days 7 and 40 post-inoculation(5)Th1 and Th2 responses against SARS-CoV-2 on day 7 post-inoculation(6)QuantiFERON SARS-CoV-2 RUO test on days 7 and 40 post-inoculation

<Efficacy>

(1)COVID-19 incidence till day 40 post-inoculation

<Safety>

(1)All adverse events occurring between days 0 and 40 post-vaccination, deaths due to adverse events, serious adverse events other than death, significant adverse events, and severe (Grade 3 or higher) adverse events(2)Physician-reported outcomes
①Specific local adverse events *1②Specific systemic adverse events *2③Unspecified adverse events *3
(3)Maximum body temperature from day 0 to day 6 post-inoculation(4)Subject-reported outcomes

*1 Specific local adverse events: erythema, swelling, induration, and pain at the injection site between day 0 and day 6 post-inoculation.

*2 Specific systemic adverse events: fever (body temperature of ≥37.5 °C, if present), headache, malaise, nausea, and myalgia between day 0 and day 6 post-inoculation

*3 Unspecified adverse events: Adverse events that do not fall into the category of specified adverse events between day 0 and day 6 post-inoculation are classified as unspecified adverse events. Erythema, swelling, induration, and pain at the injection site, pyrexia, headache, malaise, nausea, and myalgia at day 7 post-inoculation are defined as non-specified adverse events.

**Statistical analysis**
**items**

**Analysis sets**

**Study protocol-adapted analysis set (per-protocol set; PPS)**

Among the enrolled participants, subjects associated with major protocol failure and those in whom blood sampling for titration on day 7 post-immunization cannot be performed are excluded.

**Safety set**

All patients who received KD-414 will be included.

**Target sample size and rationale**

Target number of subjects receiving KD-414 to evaluate the main hypothesis: 60 subjects

Target sample size for this study: 97 patients

Rationale: Determining if the antibody titer after the booster dose (KD-414) was lower than that after the second dose of BNT162b2 mRNA. The IgG-S antibody titer after the administration of the second dose of BNT162b2 mRNA vaccine will be investigated because the data for neutralizing antibody titers evaluated using the assay used in this study are not available. The titers of IgG-S and neutralizing antibodies are reported to be highly correlated. We assume that the titer of IgG-S after immunization with KD-414 is similar to that after immunization with the second dose of BNT162b2 mRNA in this study population (4.25 (standard deviation; SD 0.35) on a log_10_ scale). The World Health Organization guidelines on vaccine development set a geometric mean titer (GMT) ratio of 0.67 as the threshold for testing non-inferiority. In the case that the lower limit of the 95% confidence interval for the GMT of IgG-S for the KD-414 to that of Pfizer vaccine is >0.67, the antibody titer after the booster of KD-414 is not inferior to the second dose of BNT162b2 mRNA. Based on these assumptions, the required sample size for 90% power would be 45 for an SD of 0.35, whereas it would be 58 for an SD of 0.4 (Table 5).

The main objective of this study is to obtain consent for immunization with KD-414 from 97 patients with titer test results up to the second dose. Although the rate of informed consent is unknown, the target sample size will be 60 to determine 58 post-vaccination titer values after immunization with KD-414. However, even if the number of subjects enrolled is below 60, a certain power will be assured.

Additionally, patients who do not agree to receive KD-414 (consented to participate in this study) will also be enrolled to compare the antibody titers of non-vaccinated subjects with KD-414 with those of vaccinated subjects. The target sample size for non-vaccinated and vaccinated cases combined will be 97 patients who participated in the previous study.

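### The only non-inferiority rule is worded for IgG-S, a secondary endpoint; the primary neutralizing-titre ratio carries no margin, and the 90% power is not established for it

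*Protocol article*

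**What the plan says.** All references are to the Protocol article, Methods.

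- **Primary endpoint:** "Neutralizing antibody titers against SARS-CoV-2 on day 7 post-immunization".
- **Secondary endpoint, immunogenicity item 2:** "IgG antibodies against SARS-CoV-2 spike protein (IgG-S) on days 7 and 40 post-inoculation".
- **Target sample size and rationale:** the planning inputs are all for IgG-S. The post-dose-2 value is "4.25 (standard deviation; SD 0.35) on a log_10_ scale". The expected effect is given as "We assume that the titer of IgG-S after immunization with KD-414 is similar to that after immunization with the second dose". The margin comes from a guideline said to "set a geometric mean titer (GMT) ratio of 0.67 as the threshold for testing non-inferiority". KD-414 is then called not inferior if the "lower limit of the 95% confidence interval for the GMT of IgG-S for the KD-414 to that of Pfizer vaccine is >0.67". From this, "the required sample size for 90% power would be 45 for an SD of 0.35", and 58 for an SD of 0.40; Table 5 adds the figures for 80% and 85%.
- **Reason given for IgG-S:** no neutralizing data from the study's assay existed at planning, and "The titers of IgG-S and neutralizing antibodies are reported to be highly correlated". No coefficient, SD or conversion is given.
- **Primary endpoint analysis:** a day-7 neutralizing geometric mean in the per-protocol set, with a ratio to the day-7 value after BNT162b2 and a 95% confidence interval. No margin and no rule for a conclusion are stated.

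**The concern.** A non-inferiority conclusion should rest on the endpoint named as primary. Here the endpoint, the analysis and the rule do not line up: the first two are neutralization, the third is IgG-S. Analysis of the secondary variables applies the primary-type analyses to IgG-S as well, so the ratio that the printed rule needs will be produced.

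If the two ratios disagree, a literal reader would call KD-414 not inferior on binding antibody although the lower limit for neutralization was below 0.67. Another reader would apply 0.67 to neutralization and conclude the opposite. The choice would then be made with both results in view.

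The power statement has a related, milder problem. It describes IgG-S, but stands as the justification for the number of subjects who are to evaluate the main hypothesis.

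**Working it through.** **1. Which titre each section uses**

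| Section | Titre | Margin or rule |
|---|---|---|
| Primary endpoint | Neutralizing, day 7 | none |
| Primary endpoint analysis | Neutralizing, day 7 ratio and 95% CI | none |
| Secondary endpoint | IgG-S, days 7 and 40 | none |
| Target sample size and rationale | IgG-S | lower 95% limit > 0.67 |

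No section carries 0.67 over to the neutralizing titre.

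**2. Does the stated reason cover the rule?**

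The reason is that neutralizing data were missing at planning. Investigation items for immunogenicity endpoints plans live-virus neutralization at days 0, 7 and 40 in this study and on residual day-7 and day-40 samples from the previous one. Handling and storage of records also provides stored sera from day 7 after dose 2 for neutralization. Both sides of the neutralizing ratio will therefore exist at analysis. The reason supports a borrowed SD. It does not support a rule on IgG-S.

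**3. Reproducing Table 5**

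Inputs: margin 0.67; true ratio 1; log10 SD 0.35 or 0.40; two-sided 95% interval, so one-sided alpha 0.025.

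Margin on the log10 scale: −log10(0.67) = 0.1739.

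A one-sample (or paired) t-test has power P(T > t(0.975, n−1)), where T is noncentral t with n−1 degrees of freedom and noncentrality 0.1739·√n / SD. The required n is the smallest that reaches the target power.

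| SD | 80% | 85% | 90% |
|---|---|---|---|
| 0.35, recomputed | 34 | 39 | 45 |
| 0.35, Table 5 | 34 | 39 | 45 |
| 0.40, recomputed | 44 | 50 | 58 |
| 0.40, Table 5 | 44 | 50 | 58 |

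All six cells match. Example for n = 58 and SD 0.40: noncentrality 0.1739 × √58 / 0.40 = 3.311, critical value 2.002, power 0.902. The figures have no arithmetic fault, and every endpoint-specific input is an IgG-S value or assumption.

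**4. What carries over to the neutralizing titre**

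The formula needs the SD of the tested log10 quantity and the true ratio. A high correlation fixes neither, because correlation does not change when one variable is shifted or rescaled. The article gives neither quantity for neutralization, so the SDs below are assumptions (n = 58, margin 0.67, true ratio 1).

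| Assumed SD | Noncentrality | Power |
|---|---|---|
| 0.35 | 3.785 | 96% |
| 0.40 | 3.311 | 90% |
| 0.45 | 2.944 | 82% |
| 0.50 | 2.649 | 74% |
| 0.60 | 2.208 | 58% |

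At a true ratio of 1, the 90% holds for neutralization if the SD is about 0.40 or less, and not otherwise. If the analysis is paired within person, the SD that matters is that of the within-person differences, which the article gives for neither assay.

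**The case against.** The strongest reply is that IgG-S is an openly declared planning proxy. The section says why it is used and sizes the study on SD 0.40 although 0.35 was observed. That is ordinary practice when the primary endpoint has no data. On this view the 0.67 sentence, which stands between the IgG-S assumption and the resulting sample size, is only the sizing hypothesis in proxy terms. The sentence ends by speaking of the antibody titre in general, the analysis sections keep neutralization primary, and no non-inferiority decision is attached to IgG-S there. The rationale for the primary endpoint also calls the study exploratory, and an unseen analysis plan may contain the missing criterion.

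Much of this stands. The proxy is disclosed, the arithmetic is right, and the sizing-hypothesis reading is possible. A margin missing from the analysis section would alone be a weak point in a condensed article. But the article does print a rule and a non-inferiority conclusion, refers to a main hypothesis, and words the rule for a secondary endpoint. The other reading has to be supplied by the reader.

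Two stronger readings are tempting and are not supported:

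- **That power for the primary endpoint is below 90%.** No neutralizing SD is given, so the direction is unknown; at SD 0.35 power would be 96%. The positivity cut-off of 40 for neutralization in Table 4 does not help, since IgG-S has a cut-off too and a cut-off says nothing about the SD of a log titre.
- **That the trial will be decided on IgG-S.** The literal wording allows this, but the analysis sections do not say it.

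**Conclusion.** The point holds as a mismatch of endpoint and rule. The one printed non-inferiority criterion names IgG-S, while the primary endpoint and its analysis are the day-7 neutralizing ratio, without a margin. This matters only if the two ratios fall on different sides of the criterion, and the protocol does not settle which one then governs.

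The figures of 45 and 58 are correct for IgG-S. Power for the neutralizing titre is not established. The illustrative span of 96% to 58% rests on 58 evaluable values, a true ratio of 1, the one-sample method that reproduces Table 5, and assumed SDs from 0.35 to 0.60. It does not show that the study is underpowered and gives no ground for a larger sample. Severity: should be fixed.

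**What to change.** 1. In Target sample size and rationale and in Primary endpoint analysis, state that non-inferiority is judged on the day-7 neutralizing GMT ratio (KD-414 divided by the second BNT162b2 dose) and is concluded if the lower limit of its 95% confidence interval is above 0.67. State that the same comparison for IgG-S is supportive.
2. Label 45, 58 and the rest of Table 5 as planning figures for IgG-S, and say that power for the neutralizing titre is not established.
3. Add one line with the illustrative power at 58 values and a true ratio of 1 for assumed SDs of 0.35 to 0.60, marked as assumptions.

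The cost is wording only. The planned samples, estimates and sample size stay as they are. The wording should be settled before the neutralizing and IgG-S results are seen.

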**Criteria for discontinuation of clinical studies**

(1)Ethical or medical reasons (including those to ensure the safety of study subjects)(2)Significant or continued non-compliance determined by the investigator or research institution(3)The Clinical Research Review Board’s decision to terminate or suspend the clinical trial during the continuation review of the ongoing trial(4)In cases where study subjects are unlikely to satisfy the inclusion criteria(5)The scientific justification for conducting this study is not satisfactory(6)The research physician has abandoned the study

**Handling of cases**

The principal investigator and the individual responsible for statistical analysis will decide on the handling of the enrolled cases after discussion. In case of a problem, the investigator and the statistical analysis manager should discuss and decide on the handling of the case. The details of the case-handling decisions will be retained in the record.

**Data handling**

In case of any doubt regarding the handling of data during data collection or analysis, the principal investigator and the statistical analysis manager will decide how to proceed after discussion. No imputation is performed for the missing data. Details, including handling outliers, are specified in the statistical analysis plan.

**Statistical analysis items and analysis plan**

The original version of the analysis plan will be generated prior to data fixation.

**Analysis of study subject background**

Background factors will be tabulated for PPS and KD-414-vaccinated and non-vaccinated cases.

**Primary endpoint analysis**

Primary analysis

The geometric mean of the neutralizing antibody titers will be calculated for PPS cases on day 7 post-inoculation. Meanwhile, the geometric mean ratio of the neutralizing antibody titer at day 7 post-BNT162b2 mRNA vaccination to the geometric mean value and the 95% confidence interval calculated in the previous study (“*A survey of vaccine-induced COVID-19 antibody titer to verify temporal change*”: NCGM Ethical Review Board Approval Number: NCGM-A-004175-04) will be used.

Secondary analysis for the primary endpoint
(1)The geometric mean of the neutralizing antibody titer on day 7 against day 0 will be calculated for PPS cases. Additionally, the geometric mean of neutralizing antibody titers in non-vaccinated subjects on day 40 will be calculated. The geometric mean ratio of neutralizing antibody titers in vaccinated subjects to that in non-vaccinated subjects among PPS cases will also be calculated.(2)The percentage of cases in which the geometric mean ratio of neutralizing titers on day 7 to those on day 0 was ≥4 will be calculated.(3)Subgroup analyses will be performed on the following items for test drug-vaccinated and non-vaccinated cases among PPS cases:

▪Work history (presence or absence of work-related contacts)▪Sex (male/female)▪Age (below or above the median)▪Medical history▪Interval between the third dose and the second dose of the BNT162b2 mRNA vaccine.▪By variant
(4)Among PPS cases, the geometric mean neutralizing antibody titer on day 7 will be calculated for unvaccinated cases. Additionally, if the non-vaccinated subject received the third dose of other vaccines, the geometric mean of neutralizing antibodies on day 7 after the third dose of other vaccines will be calculated.(5)Among PPS cases, the geometric mean neutralizing antibody titers on day 7 will be calculated for unvaccinated and vaccinated cases and compared using the Wilcoxon rank-sum test. Additionally, the geometric mean ratio of neutralizing antibodies on day 7 post-third dose of other vaccines against the vaccinated subject and the 95% confidence interval will be calculated for non-vaccinated subjects.

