**Inclusion criteria**

(1)Individuals who have received two doses of BNT162b2 mRNA vaccine and have completed the measurement of antibody titer on Day 29 (Day 7 after the second dose) in the previous study [3,4].(2)Individuals who provide written informed consent, comply with the instructions during the study period, undergo medical examination specified in the study protocol, and can report symptoms.

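### The primary comparison does not use the within-person pairing that the design offers, and Table 5 takes the SD of a single titre as the SD of the comparison, so the 90% power depends on an unstated correlation.

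*Protocol article*

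**What the plan says.** - **Primary endpoint analysis:** the geometric mean of the day-7 neutralizing titres is computed in the per-protocol set. The comparison is described as "the geometric mean ratio of the neutralizing antibody titer at day 7 post-BNT162b2 mRNA vaccination to the geometric mean value", with a 95% confidence interval, and refers to the previous NCGM study. No within-person difference is mentioned. BNT162b2 is named first in the ratio.
- **Target sample size and rationale:** the WHO guidelines "set a geometric mean titer (GMT) ratio of 0.67 as the threshold for testing non-inferiority". Non-inferiority holds if "the lower limit of the 95% confidence interval for the GMT of IgG-S for the KD-414 to that of Pfizer vaccine is >0.67", so here KD-414 comes first. The assumed IgG-S titre is 4.25 with SD 0.35 (log10), which describes one titre after dose 2. On that basis "the required sample size for 90% power would be 45 for an SD of 0.35", and 58 for an SD of 0.40. The target is 60 recipients to obtain 58 values, out of 97 people from the earlier cohort.
- The same section explains the use of IgG-S by noting that "the data for neutralizing antibody titers evaluated using the assay used in this study are not available".
- **Inclusion criteria:** participants must "have completed the measurement of antibody titer on Day 29 (Day 7 after the second dose) in the previous study".
- **Investigation items for immunogenicity endpoints:** neutralizing titres are measured on the new sera and "in the residual sample collected on days 7 and 40 in the previous studies".

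**The concern.** The same people supply both titres, yet the stated comparator is a cohort mean. That mean is an estimate, and most of those who contribute to it would also be KD-414 recipients if the target of 60 is reached. The error of the ratio therefore depends on how strongly a person's post-KD-414 titre tracks the same person's post-dose-2 titre. The plan does not say how this enters the interval, and the sample size uses an SD that ignores it.

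The 0.67 criterion is read from the lower limit of this interval. If that limit is computed with too small a standard error, non-inferiority is declared too easily. If it is computed correctly by pairing, the power may not be the 90% stated. The order of the ratio also matters: a lower limit above 0.67 means something different for BNT162b2 over KD-414 than for KD-414 over BNT162b2.

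**Working it through.** **Inputs.** From Target sample size and rationale: margin 0.67, lower limit of a 95% interval (one-sided 0.025), assumed true ratio 1, SD 0.35 or 0.40, 58 values from 60 recipients, cohort of 97. The within-person correlation (rho) is not in the document; 0, 0.3, 0.5 and 0.7 are assumed. Equal SDs at the two time points are also assumed.

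**1. Reproduce Table 5.** The distance to the margin is −log10(0.67) = 0.1739. For a one-sample t-test, power is the probability that a noncentral t with n−1 degrees of freedom and noncentrality 0.1739·√n/SD exceeds the 97.5% point of t. The smallest n is:

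| SD | 80% | 85% | 90% |
|---|---|---|---|
| 0.35 | 34 | 39 | 45 |
| 0.40 | 44 | 50 | 58 |

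All six cells match. Two independent samples would need 86 and 112 per group at 90% power (normal approximation), so that is not what was done.

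**2. When the single-titre SD is right.** The SD of a within-person difference is SD·√(2(1−rho)). It equals SD only when 2(1−rho) = 1, that is rho = 0.5. Otherwise Table 5 is right only if the reference mean has no error.

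**3. Scenario A: reference treated as error-free.** Take 60 recipients inside a 97-person reference. The variance of the difference in means is SD²·[1/60 + (1−2·rho)/97], against the SD²/60 that would be used. The ratio of true to used standard error is √(1 + 60(1−2·rho)/97). Coverage is 2Φ(1.96/ratio) − 1.

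| rho | SE ratio | coverage | one-sided error |
|---|---|---|---|
| 0 | 1.272 | 87.7% | 6.2% |
| 0.3 | 1.117 | 92.1% | 4.0% |
| 0.5 | 1.000 | 95.0% | 2.5% |
| 0.7 | 0.868 | 97.6% | 1.2% |

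Using t in place of normal quantiles moves coverage by about 0.2 points.

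**4. Scenario B: paired analysis, 58 values.** The formula of step 1 is used with the SD of the difference from step 2.

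| rho | SD of difference (0.35 / 0.40) | power (0.35 / 0.40) |
|---|---|---|
| 0 | 0.495 / 0.566 | 75% / 63% |
| 0.3 | 0.414 / 0.473 | 88% / 79% |
| 0.5 | 0.350 / 0.400 | 96% / 90% |
| 0.7 | 0.271 / 0.310 | 99.8% / 99% |

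With 60 values, 90% power is reached from about rho 0.32 (SD 0.35) or 0.48 (SD 0.40).

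**The case against.** The strongest defence is that the text never says the reference is a constant or that the comparison is unpaired. The sentence is unclear, and its mention of a 95% interval from the previous study may point to the reference's own uncertainty. Table 5 cannot decide the matter, because a paired t-test with a difference SD of 0.35 or 0.40 gives the same six numbers. The planned assay of residual sera fits a paired intention. This stands: an error-free reference is an inference from the two sections. It does not clear the plan, because the SD is given alongside the mean of one titre and nothing supports it as the SD of a difference.

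The study is also described as exploratory, and 60 recipients at SD 0.35 leave some reserve. Both are true, and they limit the size of the problem.

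Three further inferences are tempting but not supported:
- A reader might infer that the reference titres will be on a different assay scale. The statement that such data are lacking explains the sizing on IgG-S. The residual sera are to be tested for neutralization at the same department as the new sera. What remains is that the analysis section should say which values it uses.
- A reader might infer that all inference in the trial rests on this interval. The secondary analyses of the primary endpoint include a Wilcoxon test and another ratio with an interval.
- A reader might infer a definite selection bias from comparing consenting, screened recipients with the whole cohort. The text does not say that non-recipients enter the reference, and neither size nor direction can be derived.

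**Conclusion.** The point holds in a limited form. The stated primary comparison does not use the pairing, and the 90% power rests either on an error-free reference or on an unstated difference SD equal to the cross-sectional SD.

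A reader might conclude that the interval and the power are valid only at a correlation of exactly 0.5. That goes too far: above 0.5 the interval is conservative and paired power exceeds 90%. The harm lies below about 0.5 (below about 0.3 for power with 60 people at SD 0.35).

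Nor do the coverage loss and the power loss occur together. With an error-free reference, n = 60 within 97 and rho 0, the chance of declaring non-inferiority at a true ratio of 1 is Φ((0.1739·√60/SD − 1.96)/1.272), about 93% (SD 0.35) or 87% (SD 0.40). The price is a one-sided error of 6.2% in place of 2.5%. The fall to 75% or 63% at rho 0 belongs to the paired analysis of 58 values.

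All sizes depend on assumed correlations, on equal SDs, and on the plan's own step of carrying the IgG-S SD over to neutralizing titres. Scenario A further assumes that the 97-person reference contains the 60 recipients.

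**What to change.** 1. In Primary endpoint analysis, define for each recipient d = log10(day-7 KD-414 titre) − log10(own day-7 post-dose-2 titre), the second value coming from the assay of that person's residual serum. Report the mean of d with a paired-t 95% interval, back-transformed to the ratio KD-414/BNT162b2. Conclude non-inferiority if the lower limit exceeds 0.67.
2. Correct the order of the ratio there so that it agrees with Target sample size and rationale.
3. Recaption Table 5 as sample sizes for an SD of the within-person difference of 0.35 or 0.40, and add power over a range of correlations, as in step 4 of the working.

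The cost is wording and one table, with no new participants or visits. There are two downsides. The stated power becomes conditional on the correlation. Recipients without enough residual serum also drop out of the paired set, because the inclusion criterion requires a completed titre measurement rather than stored serum, and missing data are not imputed. The number with usable residual serum should be checked before the paired sample size is stated.
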